#### Qualitative analysis

Interviews and focus groups will be audio recorded, transcribed and checked by the researcher. Standard thematic analysis techniques will be employed. Transcripts will be closely examined to identify themes and categories [102]. Codes will be applied to these broad themes which will then be broken down further into sub-codes. Agreement on concepts and coding will be sought between members of the research team to ensure reliability. Commonly expressed themes will be identified as well as unusual cases. 20% of the data will be coded separately by two team members to check reliability of the coding process. Interviewing will be iterative; where new themes emerge they will be incorporated into the interviews and focus groups. Thematic analysis will be supported by qualitative analysis software (NVIVO).

#### Economic analysis

As training can be regarded as an investment producing a flow of benefits over time, training costs will be amortised and expressed in equivalent annual cost terms. Costs of delivering the intervention, including an element for training, will be apportioned to the intervention group. Mean differential costs between intervention and control groups will be estimated. As cost data are often skewed, tests for normality will be carried out and if data are not normally distributed non-parametric analyses will be used to carry out the comparison of costs between the two arms of the trial. Economic comparisons between the two study arms will take account of the cluster nature of the data.

Results of the cost utility analysis will be reported in the form of an incremental cost utility ratio (incremental cost/QALY). A series of one-way sensitivity analyses will assess how sensitive results are to changes in key assumptions. Probabilistic sensitivity analyses will be used to quantify uncertainty around the estimates and cost effectiveness acceptability curves will show the probability of the intervention having an incremental cost utility ratio below a range of acceptability thresholds [103].

In the secondary analysis, cost effectiveness will be assessed using BMI as the effectiveness measure. Unless the intervention is shown to be dominant (lower costs greater effect) the resulting incremental cost effectiveness ratio (incremental cost per unit difference in BMI) can be compared with that of other weight management programmes delivered to pregnant women.

Exploratory work will be carried out to model the medium term effect of the intervention bearing in mind the high degree of uncertainty in long term weight patterns particularly among the obese [104].

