### Economic evaluation

The main evaluation will be a cost utility analysis assessing between group differences in total costs against differences in Quality Adjusted Life Years (QALY) derived from the EQ-5D quality of life instrument [88]. This approach is preferred by the National Institute for Health and Care Excellence (NICE) for the economic evaluation of NHS interventions as resulting cost utility estimates can be compared across unrelated health care interventions (http://www.NICE.org.uk). However, as a generic measure, EQ-5D may not be sufficiently sensitive to capture small changes in health-related quality of life in essentially healthy participants. A secondary cost effectiveness analysis will therefore be undertaken with BMI as the effectiveness measure. Both analyses will be done from an NHS perspective but as the HELP intervention might substitute for other weight control interventions, patient borne costs will also be assessed but will be reported separately.

Resources for training intervention midwives and delivery of the intervention will be recorded prospectively in relevant units and valued using standard methods [96]. Participants’ use of NHS resources will be collected by questionnaire from women in both arms of the trial at baseline and all follow-up points specified above and similarly valued. The questionnaire will also record payments for non-NHS weight loss/maintenance activities and will include the EQ-5D questionnaire [88].

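### A normality test decides how costs are compared, and the unnamed non-parametric fallback, if a rank test, would not test the mean cost difference behind the cost-utility ratio

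*Protocol article*

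**What the plan says.** All the relevant text is in the protocol article, mostly under Economic analysis.

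- **The quantity to be estimated**, stated without condition: "Mean differential costs between intervention and control groups will be estimated".
- **The trigger:** "As cost data are often skewed, tests for normality will be carried out".
- **The branch:** "if data are not normally distributed non-parametric analyses will be used to carry out the comparison of costs". No procedure is named.
- **Clustering**, in the next sentence: "Economic comparisons between the two study arms will take account of the cluster nature of the data".
- **The result that costs feed:** "Results of the cost utility analysis will be reported in the form of an incremental cost utility ratio (incremental cost/QALY"). Under Economic evaluation the main analysis is a "cost utility analysis assessing between group differences in total costs against differences in Quality Adjusted Life Years (QALY").
- **Uncertainty around the ratio:** "Probabilistic sensitivity analyses will be used to quantify uncertainty around the estimates", together with acceptability curves.

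**The concern.** The article states a decision rule here, so this is more than a detail left to a later document. There are two difficulties.

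First, the trigger decides almost nothing. Costs in a maternity population are skewed, as the protocol accepts, and at this sample size a normality test will detect quite mild skewness. The non-parametric branch is therefore the one that will be used.

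Second, the branch sits uneasily with the purpose of the analysis. A non-parametric comparison chosen after a failed normality test would ordinarily be read as a rank test. A rank test asks whether costs in one arm tend to be higher than in the other. It does not test the difference in arithmetic means, and that difference is the numerator of the incremental cost per QALY. The published cost comparison and the published ratio could then point in different directions. For example, a small number of very expensive births could raise one arm's mean considerably while a rank test showed nothing.

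**Working it through.** The protocol gives no cost mean, SD or cost-based sample size, so there is no stated figure to reproduce. The check has two parts: reading the sentences together, and an illustration on assumed costs.

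**1. The text under its two readings**

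| Reading of the fallback | Agrees with estimating mean differential costs? | Does the normality trigger serve a purpose? |
|---|---|---|
| Rank test | No: it tests a different quantity | Yes, but it leads away from the mean |
| Bootstrap of the mean difference | Yes | No: this bootstrap needs no normality test to justify it |

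Under either reading the sentence needs correcting, and naming the procedure would not be enough.

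**2. Inputs for the illustration**

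- Women analysed: 400 in 20 units (Sample size section), 10 units per arm, so 400 / 2 = 200 per arm.
- Cost distribution: lognormal. This is an assumption, and so are the medians and log-SDs below.
- Clustering is left out, because the question is only which quantity each test addresses.

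**3. How often would the trigger fire?**

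Shapiro-Wilk test at 5% on simulated lognormal costs:

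- n = 400: rejects in about 99% of samples at log-SD 0.2, and in 100% at 0.3 and 0.5.
- n = 200: rejects in 99.4% at log-SD 0.3, and in 100% at 0.5 and 1.0.

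A log-SD of 0.2 or 0.3 is mild skewness. The fallback is close to certain.

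**4. Equal medians, different means**

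Both medians are £2,000, with log-SD s = 1.0 in one arm and 1.2 in the other. Mean = 2000 × exp(s²/2):

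- s = 1.0: 2000 × exp(0.50) = £3,297
- s = 1.2: 2000 × exp(0.72) = £4,109
- Difference: £811 (from unrounded means)

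Rejection rates at 5%, 200 per arm, 3,000 or more simulated trials per run:

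- Mann-Whitney: about 5% (4.9% to 5.6% across separate runs), which is chance level.
- Welch test of means: about 25% (25% to 27%).

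Analytic check on the test of means. SD = mean × √(exp(s²) − 1), giving 3,297 × √(e^1.00 − 1) ≈ £4,322 and 4,109 × √(e^1.44 − 1) ≈ £7,374. The standard error is √(4,322²/200 + 7,374²/200) ≈ £604. The ratio is 811 / 604 ≈ 1.34, so power is about 27%, in line with the simulation.

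**5. Equal means, different medians**

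Log-SD 0.8 and 1.0, with log-means 7 − 0.32 and 7 − 0.50, so both means equal exp(7) ≈ 1,097. The medians are exp(6.68) ≈ 796 and exp(6.50) ≈ 665. With 200 per arm:

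- Mann-Whitney rejects in about 48% of trials.
- Welch test of means rejects in about 5%.

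The disagreement can therefore go either way: no signal where means differ, or a frequent signal where they do not.

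**The case against.** The strongest reply is that the section already protects the mean. It commits to estimating mean differential costs before it mentions normality, and nothing in it feeds a rank statistic into the ratio. Probabilistic sensitivity analysis and acceptability curves carry the uncertainty around the ratio. A bootstrap of the mean difference is also non-parametric, and it fits the neighbouring sentences better than a rank test does. This stands. A reader might infer that mean costs will not be compared at all, or that the ratio loses its numerator. The text does not support that.

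A reader might also infer that the fallback contradicts the promise to allow for clustering, because a standard rank test ignores maternity units. That does not follow either. The clustering sentence covers all economic comparisons between arms, a non-parametric one included, so inflated error rates calculated for an unclustered rank test would describe an analysis that the plan rules out.

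Two further points carry some weight. The equal-medians example is chosen to defeat a rank test, and a test of means would also miss the £811 difference about three times in four. The example therefore shows that the two tests address different quantities; it does not show that a test of means is well powered. Also, a journal article need not name every procedure, and a fuller economic plan may do so. But the article does more than leave the method open: it fixes a trigger and a branch, and a fuller plan would have to alter that sentence as well as add to it.

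**Conclusion.** The point holds as a limited defect in a stated rule. A normality test that is almost sure to fail directs the cost comparison to an unnamed non-parametric method. If that method is a rank test, the reported between-arm cost comparison would not address the mean difference in the incremental cost per QALY and could disagree with it in either direction. If it is a bootstrap of means, the quantity is right and the normality test is superfluous. The estimated mean cost difference, the ratio and the commitment on clustering are unaffected under both readings.

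The size depends on the assumed cost distributions: about 5% against about 25% rejection when medians are equal and means differ by £811, and about 48% against about 5% when means are equal and medians differ. Other distributions would give other figures. That the normality test will almost always fail is more secure, since it holds even at mild skewness. The primary BMI analysis is not touched; the matter concerns the main economic evaluation.

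**What to change.** Delete the normality tests and the conditional non-parametric branch. State that arithmetic mean costs are compared between arms whatever their distribution, and that confidence intervals come from a method that respects maternity units. Suitable choices include a two-stage bootstrap (units, then women within units) of cost-QALY pairs, or a multilevel or generalised linear model giving the difference in mean cost. The choice among these can be left to the economic analysis plan, provided that it is made before the cost data are seen by arm.

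The cost is one sentence of wording and modest extra programming. Data collection and sample size do not change.

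### As worded, the acceptability curve's ratio-below-threshold criterion counts higher-cost, fewer-QALY draws as cost-effective; define the curve by net benefit instead

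*Protocol article*

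**What the plan says.** Under Economic evaluation, the protocol article makes the cost utility analysis the main evaluation, with QALYs from EQ-5D. It adds the caution that "EQ-5D may not be sufficiently sensitive to capture small changes in health-related quality of life in essentially healthy participants", and for that reason plans a secondary cost-effectiveness analysis on BMI.

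Under Economic analysis, the main result is to be given as incremental cost per QALY. On uncertainty it says: "Probabilistic sensitivity analyses will be used to quantify uncertainty around the estimates". The same sentence continues that "cost effectiveness acceptability curves will show the probability of the intervention having an incremental cost utility ratio below a range of acceptability thresholds", and cites a method reference. On costs: "Costs of delivering the intervention, including an element for training, will be apportioned to the intervention group".

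Dominance appears once, for the BMI analysis: "Unless the intervention is shown to be dominant (lower costs greater effect) the resulting incremental cost effectiveness ratio" can be compared with that of other programmes. The article does not mention net benefit, or how results with higher cost and less effect are handled in either analysis.

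**The concern.** A ratio of incremental cost to incremental QALYs does not rank results once the QALY difference can be negative.

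- **Higher cost, fewer QALYs (dominated).** The ratio is negative, so it lies below every positive threshold. The worst possible result is scored as a success.
- **Lower cost, fewer QALYs.** A small ratio here means little money saved per QALY lost. A ratio below the threshold should count against the intervention, but it is scored in its favour, and the reverse.

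This does no harm when nearly all draws show a QALY gain. The article gives reason to think that may not be so: it doubts that EQ-5D will pick up small changes in this population, and it charges delivery and training to one arm. If the QALY difference straddles zero and those costs are not offset, many draws will be dominated. The curve is the threshold-based summary of uncertainty for the main economic evaluation, so an inflated curve would bear directly on how the intervention is judged.

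The BMI sentence has a related gap. It sets aside the ratio only when the intervention is dominant and is silent on the mirror case of higher cost with less effect, where the ratio is equally uninterpretable.

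**Working it through.** The article gives no figure for the curve, so there is none to reproduce. The check compares the stated criterion with the net-benefit criterion on the same draws.

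**Inputs from the protocol article (Sample size):** 400 analysed women in 20 units of 20, ICC 0.02. Design effect = 1 + 19 × 0.02 = 1.38 (stated, rounded, as 1.4).

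**Assumed inputs, none in the document:** QALY SD 0.15 (range 0.10 to 0.20); cost SD £1,500; mean extra cost £300 (range £100 to £500); threshold £20,000; normal, uncorrelated cost and QALY differences; the same design effect for costs and QALYs as for BMI.

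**Standard errors.** SE = SD × √(4/400 × 1.38) = SD × 0.1175. This gives 0.0176 for QALYs and £176 for cost.

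**Criteria.** With C the incremental cost, E the incremental QALYs and L the threshold:
- literal: P(C/E < L)
- net benefit: P(L × E − C > 0)

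**Analytic check of net benefit, no QALY effect.** The SE of L × E − C is √((20,000 × 0.0176)² + 176²) ≈ £394, so the probability is Φ(−300/394) ≈ 22%.

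**Where the gap comes from (no QALY effect, £20,000).**

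| Draw | Share | Literal | Net benefit |
|---|---|---|---|
| Higher cost, fewer QALYs | 47.8% | success | failure |
| Lower cost, more QALYs | 2.2% | success | success |
| Higher cost, more QALYs, ratio below L | 19.7% | success | success |
| Lower cost, fewer QALYs, ratio below L | 1.9% | success | failure |
| Lower cost, fewer QALYs, ratio above L | 0.4% | failure | success |

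Literal: 47.8 + 2.2 + 19.7 + 1.9 = 71.6%. Net benefit: 2.2 + 19.7 + 0.4 = 22.3%. Nearly all of the gap is dominated draws.

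**By true QALY difference (£300 extra cost, £20,000).**

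| True QALY difference | Literal | Net benefit |
|---|---|---|
| −0.04 | 99% | 0.3% |
| −0.02 | 91% | 4% |
| 0 | 72% | 22% |
| +0.02 | 73% | 60% |
| +0.04 | 91% | 90% |

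Over the assumed ranges of QALY SD and extra cost, no QALY effect gives 54% to 87% literal against 4% to 42% by net benefit.

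**Sensitivity to cost-QALY correlation (no QALY effect, £300, £20,000).** Correlation 0.3: 68% against 19%. Correlation 0.5: 66% against 16%. At £1,000 with correlation 0.3, the literal curve is 49% with £300 extra cost and 43% with none.

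**BMI analysis.** With no true BMI effect and independent costs, P(dominated) = 0.5 × Φ(300/176) ≈ 48% (36% at £100, 50% at £500). P(dominant), the only case set aside, is 0.5 × Φ(−300/176) ≈ 2%.

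**The case against.** The strongest reply is that the sentence is the usual one-line description of an acceptability curve. It comes with a method reference, in an article that condenses a fuller protocol. How draws are scored is commonly left to that document or to the SAP, neither of which is at hand. This stands to the following extent. A reader might infer that the analysts will count dominated draws as successes and could report a harmful intervention as probably cost-effective. The article does not say so, and the curve would not appear alone: differences in costs and QALYs, the ratio and one-way sensitivity analyses are also planned, and a QALY loss would show there. What remains is that the article does state a criterion, and the criterion as stated is wrong outside the case of a QALY gain.

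A reader might also infer that the literal curve exceeds 50% at every threshold when there is no effect. That is not general: with uncorrelated differences it is 50% at £0, and with positive correlation it falls below 50% at low thresholds, as the figures at £1,000 show.

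Three further points are fair. The EQ-5D remark is a caution, not a forecast of a null QALY difference. A net extra cost is also assumed: the Rationale says that an effective intervention would lower health service costs, and Economic evaluation says that it might replace other weight control interventions. And for BMI, the text says only that the ratio can be compared with other programmes, which permits but does not require reporting it when dominated.

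**Conclusion.** The point holds as a defect of the stated criterion, not as proof of what will be computed. Applied literally, it counts higher-cost, fewer-QALY draws as cost-effective and misscores lower-cost, fewer-QALY draws. On the assumed inputs the overstatement at £20,000 is about 49 percentage points with no QALY effect (72% against 22% before rounding the difference) and about 87 points with a 0.02 QALY loss (91% against 4%). It shrinks to about 1 point with a 0.04 gain. These figures illustrate the mechanism; they rest on assumed SDs, extra cost, correlation and threshold, and the size moves with each. The BMI part is smaller: only dominance is set aside, and only in that analysis.

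**What to change.** In the Economic analysis section, define the acceptability curve as the proportion of draws in which threshold × incremental QALYs − incremental cost is greater than zero. In both the QALY and the BMI analyses, give no ratio when the intervention is dominant or dominated, and say which it is. For BMI, define effect as BMI reduction, so that a positive value is a benefit. It would help to report the mean incremental net benefit with its 95% interval and the share of draws in each quadrant.

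The cost is one or two sentences. The same draws are used and no new data are needed. The reported probability of cost-effectiveness may be less favourable. If the full plan already scores draws this way, the change only brings the article into line with it.

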## Discussion

This trial will evaluate the effectiveness of a theory-based intervention for obese pregnant women, which combines dietary expertise from Slimming World, physical activity, and clinical advice and supervision from midwives. The intervention aims to provide support to enhance motivation and equip women with the necessary knowledge and skills to enable them to make healthier choices and control their weight gain during pregnancy as well as maintain a healthy lifestyle postpartum through healthy eating and physical activity.

The study is novel as, to our knowledge, no RCTs of pregnancy or postpartum weight control interventions have included an assessment of cost effectiveness and there are no published trials of diet and physical activity interventions that run through pregnancy and into the postpartum period [34]. In addition, few trials have explicitly described the theoretical basis of the intervention or measured the psychological mediators of the effect.

The cluster design was chosen to avoid the risk of contamination, because midwives trained in the use of the intervention could potentially use aspects with control participants and pregnant women resident in the same area often know one other and could share study information. Also in order to run effective groups the cluster design is superior in terms of recruiting sufficient numbers to ensure sessions can be delivered locally.

The study incorporates economic and process evaluations as well as explicit testing of the theory of the intervention. The process evaluation will allow us to explore the impact of different aspects of the intervention and if the trial does not show an effect it will allow us to explore possible reasons for this.

### Protecting against bias

Staff in maternity units who volunteer for the study are likely to be motivated in favour of the intervention, which may result in disappointment in those subsequently allocated to the control group. In order to avoid differential dropout between the experimental and control groups, we will offer the maternity units in the control group the opportunity to complete the training programme after the follow-up period, should the intervention prove to be successful. Careful characterisation of the participating sites, clinicians and patients will be undertaken to judge the external validity of the study findings.

Outcome data will be collected by PIs or trained researchers allied to the project. Due to the nature of the study, it will be difficult for researchers collecting outcome data to be blinded to the allocation of the women; however no staff involved in delivering the intervention will collect follow-up data.

The findings of this study will advance current knowledge in this field, both in terms of weight management interventions for obese pregnant women as well as behaviour change theory. If the trial is successful, this could alter the management of obese pregnant women within the NHS. Potential outcomes of the intervention may include fewer complications in pregnancy and postpartum for both mother and baby as well as less traumatic deliveries. Improvements in the women’s physical and psychological health and self-esteem may also result from attendance at the intervention group sessions, and from the physical activity aspect of the intervention, independent of any weight loss. Benefits to the women may be long lasting. There is evidence that many women retain weight gained during pregnancy. If this intervention is successful this may impact on cumulative obesity developing over several pregnancies. Women will also benefit from expanded healthcare choices (e.g. midwife as opposed to consultant led care) in subsequent pregnancies, if a healthy lifestyle leads to a BMI within normal limits.

